#### 5.1.1 Oral vinorelbine

Oral ondansetron may be used as prophylactic anti-emetic before administration of vinorelbine on CSV. Full blood counts will be required on Days 1,8,15 of cycle 1 and days 1 and 8 of each subsequent cycle prior to vinorelbine dosing for patients on CSV, and days 1,8, 15 of cycle 1 and day 1 only of every subsequent cycle on MSV. On CSV, for patients who have respond or stable at disease, vinorelbine will be discontinued after 6 cycles. Full blood count is not required for day 8 of cycle 7 and subsequent cycles.

#### 5.1.2 Erlotinib

None

### 5.2 Definition of Dose-Limiting Toxicity

All toxicities will be graded according to the National Cancer Institute Common Toxicity Criteria (NCI CTC version 3). In particular, the following toxicities which tend to be more common with vinorelbine use will be recorded in detail: constipation, haematologic toxicities (neutropenia, thrombocytopenia, anemia), neutropenic infections, infections including pneumonia, urinary tract infection, bacteremia, hepatobiliary sepsis; pneumonitis; ileus; hepatitis; fatigue, weight loss, nausea and vomiting.

Hematological Dose Limiting Toxicity (DLT) is defined as follows: grade 4 neutropenia of >7 days duration, neutropenic fever, grade 4 anemia or grade 3-4 thrombocytopenia that occurs during the first cycle of treatment.

Non-hematologic DLT is defined as any grade 3 or grade 4 non-hematologic toxicity that occurs during the first cycle of treatment.

Any toxicity causing a total of 14 days delay will also be considered dose limiting. Toxicities will be classified as related to the study drug unless they were attributable to either underlying tumour progression, concurrent medical condition or a concomitant medication. Any unusual toxicities must be reported to the Principal Investigator

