## **Neurological**

Neurosensory disorders were generally limited to loss of deep tendon reflexes (Grades 1 to 2: 12.4%) and infrequently severe. One patient presented partially reversible grade 3 ataxia. Neuromotor disorders were seen in 10.0% of patients (Grade 3: 1.0%). Neuroconstipation was seen in 11.3% of patients (Grades 1 to 2: 10%) and rarely progressed to paralytic ileus (1.4%). One episode of fatal paralytic ileus was reported. Use of prescription laxatives may be appropriate in patients with prior history of constipation and/or who received concomitant treatment with opioid analgesics. Mild to moderate peripheral neuropathy manifested by paraesthesia and loss of deep tendon reflexes (Grade 3: 2.5%, Grade 4: 0.2%) and hyperesthesia have been reported with IV administration. After prolonged treatment, weakness of the lower extremities has also been reported. The effects are dose dependent but usually reversible when treatment is discontinued.

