### **Warnings**

#### **Pulmonary Toxicity**

There have been infrequent reports of serious Interstitial Lung Disease (ILD)-like events, including fatalities, in patients receiving TARCEVA for treatment of NSCLC, pancreatic cancer or other advanced solid tumors. In the randomized single-agent NSCLC study, the incidence of ILD-like events (0.8%) was the same in both the placebo and TARCEVA groups. In the pancreatic cancer study - in combination with gemcitabine, the incidence of ILD-like events was 2.5% in the TARCEVA plus gemcitabine group vs. 0.4% in the placebo plus gemcitabine group.

The overall incidence of ILD-like events in approximately 4900 TARCEVA-treated patients from all studies (including uncontrolled studies and studies with concurrent chemotherapy) was approximately 0.7%. Reported diagnoses in patients suspected of having ILD-like events included pneumonitis, radiation pneumonitis, hypersensitivity pneumonitis, interstitial pneumonia, interstitial lung disease, obliterative bronchiolitis, pulmonary fibrosis, Acute Respiratory Distress Syndrome and lung infiltration. Symptoms started from 5 days to more than 9 months (median 39 days) after initiating TARCEVA therapy. In the lung cancer trials most of the cases were associated with confounding or contributing factors such as concomitant/prior chemotherapy, prior radiotherapy, pre-existing parenchymal lung disease, metastatic lung disease, or pulmonary infections.

In the event of an acute onset of new or progressive, unexplained pulmonary symptoms such as dyspnea, cough, and fever, TARCEVA therapy should be interrupted pending diagnostic evaluation. If ILD is diagnosed, TARCEVA should be discontinued and appropriate treatment instituted as needed

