| Erlotinib                  | To be taken whole half hour before breakfast                                                                                                                                                     | Dose as appropriate for assigned dose level | Oral         | Daily                                                                                                                                |                     |

In cases where the patient's BSA > or equal to 2.0, oral Navelbine dose should not exceed twice the dose/m^2 (e.g. 120 mg for 60 mg/m^2, and 160 mg for 80 mg/m^2) per week. In cases where the BSA < or equal to 1.4, these patients will not be recruited into the metronomic arm – this is for patient safety to avoid excessive dose.

The standard “3+3” rule will be employed for dose escalation. Three patients will be accrued at the starting dose levels. If no dose limiting toxicities greater than grade 2 were observed, 3 patients would be entered at the next dose level. If, at any dose level, one of the first 3 patients experiences a DLT, 3 additional patients will be entered at that dose level. If 2 out of 6 patients experience dose-limiting toxicities at this dose level, dose escalation will cease.

The maximally tolerated dose (MTD) will be defined as one dose level below that at which 2 or more patients experienced DLT. If DLT is observed at initial level of either schedule, an additional 3 patients will be accrued at the –1 level. If DLT is observed at this level, the trial will be terminated.

A patient who experiences any DLT will be allowed to continue treatment with a one dose level reduction if the toxicity resolves within 14 days. If this patient experiences a DLT at the lowered dose level, study treatment will be stopped for this patient.

No intra-patient dose escalation will be allowed. Re-entry of a patient accrued at a lower dose into a higher dose cohort will not be allowed. Accrual rate is expected to be 3-4 patients per month. Dose escalation will proceed within each cohort according to the following schedule.

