| Number of Patients with DLT at a Given Dose Level                             | Escalation Decision Rule                                                                                                                                                                                                                                                                                                                                                                                                                                           |
|-------------------------------------------------------------------------------|--------------------------------------------------------------------------------------------------------------------------------------------------------------------------------------------------------------------------------------------------------------------------------------------------------------------------------------------------------------------------------------------------------------------------------------------------------------------|
| 0 out of 3                                                                    | Enter 3 patients at the next dose level.                                                                                                                                                                                                                                                                                                                                                                                                                           |
| $\geq 2$                                                                      | Dose escalation will be stopped. This dose level will be declared the maximally administered dose (highest dose administered). Three (3) additional patients will be entered at the next lowest dose level if only 3 patients were treated previously at that dose.                                                                                                                                                                                                |

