### 7.1 Adverse Event Characteristics

- **CTCAE term (AE description) and grade:** The descriptions and grading scales found in the revised NCI Common Terminology Criteria for Adverse Events (CTCAE) version 3.0 will be utilized for AE reporting. All appropriate treatment areas should have access to a copy of the CTCAE version 3.0. A copy of the CTCAE version 3.0 can be downloaded from the CTEP web site (<http://ctep.cancer.gov>).
- **‘Expectedness’:** AEs can be ‘Unexpected’ or ‘Expected’ (see Section 7.1 above)

for expedited reporting purposes only. ‘Expected’ AEs (the ASael) are ***bold and italicized*** in the CAEPR (Section 7.1.1).

- **Attribution** of the AE:
  - Definite – The AE *is clearly related* to the study treatment.
  - Probable – The AE *is likely related* to the study treatment.
  - Possible – The AE *may be related* to the study treatment.
  - Unlikely – The AE *is doubtfully related* to the study treatment.
  - Unrelated – The AE *is clearly NOT related* to the study treatment.

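### Section 5.2 closes the non-haematologic DLT definition at grade 4 while Section 5.1 sets no upper grade, so a related cycle 1 toxicity recorded only as fatal does not enter the DLT count as written

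*Protocol*

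**What the plan says.** Section 5.2 of the protocol is the only place where a DLT is defined. It gives three routes:

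- Haematologic: "grade 4 neutropenia of >7 days duration, neutropenic fever, grade 4 anemia or grade 3-4 thrombocytopenia that occurs during the first cycle of treatment".
- Non-haematologic: "Non-hematologic DLT is defined as any grade 3 or grade 4 non-hematologic toxicity that occurs during the first cycle of treatment".
- Delay: "Any toxicity causing a total of 14 days delay will also be considered dose limiting".

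The same section treats toxicities as related to study drug unless tumour progression, a concurrent condition or a concomitant medication explains them. For grading, Section 7.1 says: "The descriptions and grading scales found in the revised NCI Common Terminology Criteria for Adverse Events (CTCAE) version 3.0 will be utilized for AE reporting".

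Section 5.1 uses the definition twice. In the text: "If no dose limiting toxicities greater than grade 2 were observed, 3 patients would be entered at the next dose level". In the decision table, the only input is the column headed "Number of Patients with DLT at a Given Dose Level".

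The background in Section 2.1 shows that fatal non-haematologic toxicity is foreseen with each drug. For oral vinorelbine: "One episode of fatal paralytic ileus was reported". For erlotinib: "There have been infrequent reports of serious Interstitial Lung Disease (ILD)-like events, including fatalities".

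**The concern.** Two sentences that should describe the same set of events have different upper ends. Section 5.1 is open above grade 2. Section 5.2 stops at grade 4 for non-haematologic toxicity and does not mention death. Section 5.2 supplies the definition, so its limit governs the count.

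That count does two jobs. It decides whether the next three patients go to a higher dose level, and it determines the MTD, which is the primary objective (Sections 1.1, 5.1 and 13.1). If a related death is left out, a cohort can be read as free of DLTs when its worst outcome was fatal. Elsewhere in the trial rules, deaths from toxicity appear in the serious adverse event definition (Section 12.3) and in expedited reporting (Section 7.2). Neither holds escalation.

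**Working it through.** The plan has no figure to reproduce here. The check is a reading of the sections against each other, followed by the decision table.

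**Step 1: can a fatal cycle 1 toxicity reach the count by another route?** Grade 5 is taken here as the grade for death. The protocol does not print the scale, and the argument needs only that a death is not graded 3 or 4.

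| Event in cycle 1, related | Route in Section 5.2 | Counted? |
|---|---|---|
| Fatal neutropenic fever | Neutropenic fever, listed with no grade limit | Yes |
| Non-haematologic event recorded at grade 3 or 4, then fatal | Grade 3 or 4 toxicity that occurs in the cycle; the worst grade is not asked for | Yes |
| Non-haematologic event recorded only as fatal | Not grade 3 or 4; the delay clause speaks of delay, and a death ends treatment | No, by the letter |

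The third row is the gap.

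**Step 2: does the patient stay in the denominator?** Section 11.1.1 makes every patient evaluable for toxicity from the first vinorelbine dose. The patient therefore remains one of the three, without a DLT.

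**Step 3: apply the decision table in Section 5.1.**

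| Cohort data | Count as written | Action | Count with grade 5 included | Action |
|---|---|---|---|---|
| 1 of 3 fatal only, no other DLT | 0/3 | Next level | 1/3 | Enter at least 3 more |
| 2 of 3 fatal only, no other DLT | 0/3 | Next level | 2 | Stop escalation |
| 1 of 3 with a grade 3–4 DLT, then 1 of the next 3 fatal only | 1/3, then 0/3 | Next level | 1/3, then 1/3 | Stop escalation |

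The decision changes in every row.

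**Step 4: can such an event fall in the window?** Section 2.1.2 puts the onset of ILD-like symptoms between 5 days and more than 9 months after starting erlotinib, with a median of 39 days. Erlotinib starts on day 3 (Section 9.1.2) and a cycle lasts 21 days (Section 5.1). The earliest onset is about day 3 + 5 = 8, inside cycle 1. The median is about day 3 + 39 = 42, well outside it. So the event can fall in the window, but at least half of ILD-like events would start later under any grade wording.

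**Step 5: scale, on assumptions only.** The documents give no rate for the uncovered events. Suppose their rate per patient were r = 0.5% to 2%.

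- Chance of at least one in a cohort of three, 1 − (1 − r)³: 1 − 0.995³ = 1.5%; 1 − 0.98³ = 5.9%.
- Chance that a level escalates under 3+3, with per-patient DLT probability p: (1 − p)³ + 3p(1 − p)⁵. At an assumed grade 3–4 DLT rate of 20%, p = 0.20 gives 0.709 as written. With the fatal-only events added as separate patients, p = 0.205 gives 0.698 and p = 0.22 gives 0.665.

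Across this assumed range, the average effect on escalation is small. In the cohort where the event happens, the decision changes outright.

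**The case against.** The best reply is that nobody meant to exclude deaths. Section 5.1 sets no upper grade, fatal unexpected related events go to the regulator within 7 days, and investigators would almost certainly count a related death. This stands as evidence of intent, and it makes the matter a drafting defect. It does not repair the text: Section 5.1 qualifies toxicities that are already dose limiting, and regulatory reporting does not alter the count.

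It can also be said that few events are affected. That stands too. Three stronger readings are tempting and should be resisted:

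- A reader might infer that no fatal cycle 1 toxicity is a DLT. Section 5.2 counts any grade 3 or 4 toxicity that occurs in the cycle, so a fatal event with such a stage on record is already in.
- A reader might infer that fatal haematologic toxicity is lost as well. The fatal form described under Myelosuppression in Section 2.1.1 is febrile neutropenia, and neutropenic fever is a DLT without a grade limit.
- A reader might apply an assumed early death rate to the whole planned accrual of 12 to 78 patients and quote a large probability. Such a rate would include deaths that already count, and the decision is taken cohort by cohort. The documents support no figure of that kind.

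**Conclusion.** Wrong as written, with a narrow reach. Sections 5.1 and 5.2 do not match on the upper grade. By the letter of Section 5.2, a related non-haematologic toxicity in cycle 1 recorded only as grade 5 is not a DLT. Where it occurs, one patient turns expansion into escalation, and two turn a stop into escalation. The same count feeds the MTD.

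The conclusion rests on the wording alone and on taking death to be grade 5. It needs no event rate; the percentages in the working are illustrations on assumed rates. A reader might also infer that the plan set out to escalate past deaths. The open upper end in Section 5.1 points the other way.

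**What to change.** Reconcile Section 5.1 with Section 5.2, so that Section 5.2 states explicitly how a grade 5 non-haematologic toxicity in cycle 1 enters the DLT count and the escalation sentence in Section 5.1 describes the same set of events. The attribution sentence already in Section 5.2 can separate deaths due to tumour progression, a concurrent condition or a concomitant medication, so no new attribution rule is needed. The content of the rule is for the sponsor and investigators to settle; the requirement is that both sections state it alike.

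The cost is one phrase in Section 5.2 and a matching edit in Section 5.1. Cohort sizes, the structure of the decision table and the planned accrual do not change.

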### **Myelosuppression**

Neutropenia is dose-limiting. Complete blood counts with differentials should be performed and results reviewed prior to administering each dose of NAVELBINE®. Patients treated with NAVELBINE® should be frequently monitored for myelosuppression both during and after therapy. NAVELBINE® should not be administered to patients with neutrophil counts < 1500 cells/mm^3.

Patients developing severe neutropenia should be monitored carefully for evidence of infection and/or fever. If patients present signs or symptoms suggestive of infection, a prompt investigation should be carried out. (See DOSAGE AND ADMINISTRATION for recommended dose adjustments for neutropenia).

NAVELBINE® should be used with extreme caution in patients whose bone marrow reserve may have been compromised by prior irradiation or chemotherapy, or whose marrow function is recovering from the effects of previous chemotherapy (see DOSAGE AND ADMINISTRATION).

During clinical trials where treatment was initiated at a weekly dose of 80 mg/m^2 (corresponding to an IV dose of 30 mg/m^2 in terms of systemic exposure), febrile neutropenia, in some cases fatal, was encountered in about 15% of patients. Therefore, it is recommended that the starting dose should be 60 mg/m^2 and increased to 80 mg/m^2 only if the dose is tolerated (see DOSAGE AND ADMINISTRATION).

Since dose-limiting clinical toxicity is the result of depression of the white blood cell count, it is imperative that complete blood counts with differentials be obtained and reviewed on the day of treatment prior to each dose of NAVELBINE®. If the neutrophil count is below 1500 / mm^3 and/or the platelet count is between 75,000 and 100,000 / mm^3, then treatment should be delayed until recovery.

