## 5. **TREATMENT PLAN**

### 5.1 **Agent Administration**

This is a Phase I Dose-Finding Study examining the combination of vinorelbine/erlotinib. The MTD approach will be used for both phase I schedules as shown in table below. Treatment will be administered on an outpatient basis. Oral vinorelbine will be started according to two different schedules (see tables below) 2 days before starting erlotinib. A “ping-pong” phase 1 design is employed allowing each schedule to accrue sequentially at each dose level (see figure below). This design expedites accrual without compromising safety and monitoring. All accrual will start at dose level 1. When CSV level 1 has completed accrual, MSV level 1 will start accrual while waiting for CSV level 1 patients to complete their first cycle of treatment. When MSV level 1 has completed accrual, CSV level 2 will begin and the cycle repeats itself till dose level 5 or unless DLT is reached for one schedule, and so on till DLT or dose level 5 reached. Once the MTD in one schedule is reached before level 5, the other schedule will continue till the MTD or level 5 is reached

| Dose Escalation Schedule                                                                            |                                                                     |                                                      |            |
|-----------------------------------------------------------------------------------------------------|---------------------------------------------------------------------|------------------------------------------------------|------------|
| Erlotinib
100 mg
(start 2 days after
vinorelbine for
cycle 1)                   | Dose                                                                |                                                      |            |
|                                                                                                     | CSV                                                                 | MSV                                                  | Dose Level |
|                                                                                                     | Vinorelbine (mg/m 
on D1,D8 every 21
days)        | Vinorelbine
(mg/week)                             |            |

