|                                                                                                     | 30                                                                  | 80                                                   | Level -1   |
|                                                                                                     | 40                                                                  | 100                                                  | Level 1    |
|                                                                                                     | 50                                                                  | 120                                                  | Level 2    |
|                                                                                                     | 60                                                                  | 140                                                  | Level 3    |
|                                                                                                     | 70                                                                  | 160                                                  | Level 4    |
|                                                                                                     | 80                                                                  | 180                                                  | Level 5    |
| Erlotinib
150 mg
(only in the
absence of DLT at
dose level 5 of
vinorelbine) | No DLT at dose level
5 of vinorelbine
(80 mg/m  ) | No DLT at dose level
5 of vinorelbine
(180 mg) |            |

Escalation of Erlotinib dose to 150 mg OM will only start if level 5 oral vinorelbine is reached without dose-limiting toxicities with Erlotinib 100 mg OM in each schedule.

The optimal anti-angiogenic dose of oral vinorelbine given in metronomic schedule will be determined from the Circulating Endothelial Cells/Circulating Endothelial Progenitors (CEC/CEP) assays correlations.

Efficacy will be assessed every 2 cycles during maintenance treatment. Each cycle will last 21 days with a window period of 7 days. Patients on the conventional schedule of vinorelbine who respond or have stable disease, vinorelbine will be stopped after 6 cycles and erlotinib continued. Patients on the metronomic schedule of vinorelbine who respond will continue on both vinorelbine and erlotinib.

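### The 14-day-delay DLT has no cycle limit or counting start, and the protocol states no hold on escalation while a cycle 2 start is delayed by cycle 1 toxicity

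*Protocol*

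**What the plan says.** Protocol section 5.2 defines DLT in three parts. The haematological and the non-haematological clauses are each tied to events in cycle 1. The third reads: "Any toxicity causing a total of 14 days delay will also be considered dose limiting". It gives no cycle, no reference dose and no first day for the count.

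Section 5.1 describes the ping-pong design. The metronomic schedule (MSV) accrues at level 1 "while waiting for CSV level 1 patients to complete their first cycle of treatment". The trigger for the next level is then accrual: "When MSV level 1 has completed accrual, CSV level 2 will begin and the cycle repeats itself". The escalation table in 5.1 works on DLT counts (0 of 3, 1 of 3, 2 or more) and has no row for a patient whose status is still open.

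Other relevant text:

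- Section 5.1 on timing: "Each cycle will last 21 days with a window period of 7 days", and "Accrual rate is expected to be 3-4 patients per month".
- Section 5.1 on a patient with a DLT, who may continue "with a one dose level reduction if the toxicity resolves within 14 days".
- Section 5.1.1 requires blood counts on "days 1 and 8 of each subsequent cycle prior to vinorelbine dosing for patients on CSV", so for the conventional schedule (CSV) a low count is found on the day cycle 2 is due.
- Section 6 provides for delay after significant toxicity in the first cycle and removes a patient whose delay exceeds two weeks.

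**The concern.** The MTD is the primary endpoint and rests on 0, 1 or 2 DLTs among three to six patients. One reclassified patient changes the action: 0 of 3 becomes 1 of 3 (expand), or 1 of 6 becomes 2 of 6 (stop).

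The first two DLT clauses are settled when cycle 1 ends. The delay clause is not: a patient can finish cycle 1 without a DLT, fail to start cycle 2 because of cycle 1 toxicity, and become a DLT two weeks later. The next level may by then have patients on it, dosed when the level below should have been expanded or escalation stopped.

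The clause can act on its own. The neutropenia DLT needs grade 4 for more than 7 days, or neutropenic fever. The product information in section 2.1.1 says vinorelbine "should not be administered to patients with neutrophil counts < 1500" per mm³. Slow recovery from a lesser neutropenia could therefore be a DLT through the delay clause alone.

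**Working it through.** The protocol states no figure for this, so there is none to reproduce. The check is a timeline followed by an arrival calculation.

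**Timeline.** Cycle 1 runs for 21 days, so cycle 2 is due on day 22. A 14-day delay is reached on day 22 + 14 = 36, or day 35 if the first missed day counts as day 1. Cycle 1 completion is day 21. The gap is about two weeks.

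**Inputs.**
- From the protocol: 3-4 patients per month; cohorts of 3; next level of a schedule opens when the other schedule's cohort is full.
- Assumed: Poisson arrivals; a 30.4-day month; the accrual rate covers both schedules together.

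**Chance that a next-level patient enters before a cohort patient's day 36.** Expected arrivals in the 35 days after entry are 35/30.4 × 3 = 3.45 and 35/30.4 × 4 = 4.61. The first next-level entry is the 4th further arrival after the last cohort patient (three for the other schedule, then one), the 5th after the second patient and the 6th after the first.

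| Cohort patient | Probability | 3/month | 4/month |
|---|---|---|---|
| Last | P(N ≥ 4) | 0.453 | 0.675 |
| Second | P(N ≥ 5) | 0.266 | 0.488 |
| First | P(N ≥ 6) | 0.136 | 0.315 |
| Sum | | 0.856 | 1.478 |

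**Chance of exposure per cohort of three.** Let p be the chance that a patient's only DLT is a 14-day delay of cycle 2. The documents give no value, so 2%, 5% and 10% are assumed. Exposure means that a next-level patient enters before the day 36 of such a patient. Simulation with 2,000,000 runs:

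| p | 3/month | 4/month |
|---|---|---|
| 2% | 1.7% | 2.9% |
| 5% | 4.1% | 7.1% |
| 10% | 8.0% | 13.7% |

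The bound p × sum agrees: 0.02 × 0.856 = 1.7% and 0.02 × 1.478 = 3.0%; 0.10 × 0.856 = 8.6% and 0.10 × 1.478 = 14.8%.

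**Variants.**
- First-cycle completion treated as a firm gate, so that the next level also waits for the last patient's day 22: 1.6-2.8% at p = 2% and 7.7-13.1% at p = 10%. If only arrivals after opening count, the range at p = 2% is 1.4-2.3%. The gate barely helps, because this criterion matures after it.
- Only one schedule still accruing, next level opening on day 22: 2.6-3.3% at p = 2% and 12.4-15.7% at p = 10%.
- Ordinary DLTs included: a level opens directly after three patients only if none has an ordinary DLT. At an assumed 20% risk that is 0.8³ = 0.512, so 1.7-13.7% becomes about 0.9-7.0%.

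**The case against.** The strongest reply is that escalation is governed by DLT counts as well as by accrual. A patient in an unresolved toxicity delay has not clearly been scored as free of DLT, so a careful team would wait. That is fair: the protocol does not direct escalation over a pending case. But it does not state a hold either, and the only observation it mentions ends with cycle 1.

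Second, the intended scope can largely be inferred. The neighbouring DLT clauses and section 6 all speak of the first cycle. A reader might infer from the literal text that delays in cycle 3 or later count towards the MTD. Nothing in 5.2 excludes it, but the context points the other way. The defect is that 5.2 leaves the scope unstated.

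Third, a reader might use the 7-day cycle window to build a second count from day 29, reaching 14 days on day 43, so that a restart on days 36-42 would be scored both ways. The documents never link that window to the delay count, and a delay caused by toxicity most naturally runs from the day the dose was due. The point does not depend on this reading.

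Fourth, the affected group is narrow. Most severe cycle 1 toxicity is already a DLT, the product information calls neutropenia rapidly reversible, and the 1500 threshold is background text that section 6 does not repeat as a retreatment rule. The low end of the assumed rates is therefore plausible. The simulation also omits ordinary DLTs and cohort expansion, and places every delay at its latest day. This lowers the size but does not close the gap.

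**Conclusion.** The point stands as a cheap safety and clarity fix. The delay DLT is unbounded in 5.2, and for a cycle 2 start delayed by cycle 1 toxicity it is known about two weeks after the only observation point in 5.1. That follows from the text alone.

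The size rests on assumptions. With Poisson arrivals at the planned rate, the last cohort patient is overtaken before day 36 with probability 0.45-0.68. During ping-pong accrual the chance of actual exposure is about 2-14% per cohort of three at assumed delay-only rates of 2-10%. These are upper values, and roughly halve with a 20% ordinary DLT risk.

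A reader might infer that the reported MTD will be wrong. The documents do not support that: a late DLT can still be counted and the MTD corrected. What cannot be undone is the exposure of patients one level higher before it was known.

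**What to change.** In section 5.2, replace the delay sentence with:

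> For escalation and MTD purposes, a delay totalling 14 days caused by cycle 1 toxicity, counted from the scheduled dose day (day 22 for cycle 2), is a DLT; delays arising in later cycles are reported separately by dose level.

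In section 5.1, add:

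> The next level of a schedule opens only when every patient in its current cohort has completed cycle 1 and has started cycle 2, has met a DLT criterion, or has left treatment for a reason other than toxicity (a patient who leaves before completing cycle 1 without a DLT is replaced).

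The last alternative is needed because a patient who progresses or withdraws without a DLT would otherwise block escalation indefinitely.

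The cost is protocol wording plus some waiting. Escalation waits up to about two weeks when a cohort patient is on a toxicity delay, partly absorbed by accrual to the other schedule. It also sometimes waits for the last patient's day 21 with no toxicity at all, when the other schedule fills quickly. Expected arrivals in 21 days are 21/30.4 × 3 = 2.07 and 21/30.4 × 4 = 2.76, so three further arrivals within that time have probability 0.34-0.52.
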